**Figure 1. f1:**
[figure not shown]
Programme phases.

iHOST is designed to be pragmatic and work in real-world hospitals and drug treatment services. It consists of five components, which are listed below. More information is available at
https://www.lshtm.ac.uk/research/centres-projects-groups/ihost.

a) My Meds Card: A patient advocacy card designed for hospital patients who receive OST in the community. This includes information about the importance of timely OST on hospital admission, a space for prescriber and community pharmacy contact details to enable verification of the patient’s OST dose, and an advocacy helpline number (see below). Patients can give the card to hospital clinicians to facilitate OST. The card was co-produced in workshops with people who use opioids and refined in collaboration with hospital clinicians, pharmacy, and drug treatment service providers.b) A helpline for patients and hospital staff run by the drugs advocacy charity Release (
https://www.release.org.uk/). The helpline supports patients in advocating for OST access and supports hospital staff who have questions about OST.c) An online training module for hospital staff working in acute admissions and key specialties such as infection control and hepatology. The module aims to improve knowledge about opioid dependency and withdrawal and develop non-stigmatising care and communication practices. The e-learning module will be hosted on the Exchange Supplies training site with embedded attitude and knowledge evaluation measures assessed at pre- and post-completion. The module will draw on cultural safety principles to encourage practitioners to reflect on how power relations, social norms and inequity can impact health care opportunity and outcomes, including through the expression of their personal attitudes and beliefs.d) A clinical guideline for managing opioid withdrawal, including continuity of care between community and hospital prescribers, and where necessary initiation or retitration of OST. The guideline will be developed through consultations with stakeholders, including people who use drugs, hospital staff, and representatives of national organisations, and will seek to reduce procedural barriers identified through a review of existing hospital policies
^
12
^.e) An iHOST ‘champion’ role to support implementation of iHOST. The champion will support colleagues to adopt iHOST principles. iHOST champions will receive a role description, dedicated training in addition to the online module described above, and an ‘iHOST champion’ badge.

### Systematic review

We will do a systematic review of published studies that evaluate projects aiming to improve OST in acute hospital settings. This will include a structured search for studies using any design to evaluate relevant interventions and a narrative review of findings. The protocol is published on PROSPERO
^
25
^.

### Process evaluation

We will conduct a process evaluation at each site to examine intervention fidelity, acceptability, and perceived impact on practice. We will primarily use qualitative methods to explore implementation processes, intervention mechanisms and how these vary between sites.

The methods comprise:

1. Focus groups. These will be conducted before iHOST implementation with people who use opioids and hospital staff. The aim will be to develop a baseline understanding of each local context, including drug market dynamics, service accessibility for people who use drugs, hospital opioid withdrawal management practice and perceived quality of relationships between drug treatment and hospital services. One group will be held at each local community drug treatment service and intervention hospital (ie. a total of six groups).2. In-depth interviews. These will be conducted at least two months after iHOST is launched, with hospital staff and inpatients who use opioids. The aim will be to assess acceptability and fidelity of implementation. Interviews will be informed by a topic guide including perceptions of the hospital culture, experiences of the intervention, care for patients who use opioids, communications between hospital and community services, and perceptions/experiences of opioid toxicity risk.3. Observations. These will be conducted in each hospital site both prior to and during iHOST implementation. We will shadow clinical staff to observe the dynamics of care for people who use opioids in practice, and conduct observations during interview, training and focus group visits. Observations will be recorded as ethnographic field notes, with a focus on conveying detailed information about the context and culture of each hospital site and how this interacts with the iHOST implementation process.4. Measuring intervention reach. We will get the number of advocacy cards distributed from local drug treatment services, numbers accessing the helpline, and numbers accessing the online module. The champions will be asked to keep a log of activities they carry out in support of intervention delivery (with support from the local iHOST lead).

**
*Analysis*.** We will transcribe all audio-recorded interviews and focus groups. Transcripts, interview field notes, and ethnographic observations will be uploaded into
NVivo 12 for qualitative data management and analysis. We will conduct a thematic analysis, informed by constructivist grounded theory
^
26
^ principles. Grounded theory is an analytic method for studying processes, particularly useful for generating theory that can be applied in other sites and conditions. Coding will be implemented in a stepwise process, comprising open inductive coding, focused coding, category mapping, and theme development.

Qualitative data generated will take a number of forms (interviews, focus groups, ethnographic field notes), capture multiple perspectives (people who use drugs in and out of hospital, drug treatment and hospital care providers) and reflect different contexts (the three sites). We will ‘triangulate’ (compare/contrast)
^
27
^ these data to explore how and in what way the iHOST intervention works, for whom and in what context.

Measures of intervention reach will be described and assessed alongside the qualitative data to inform understandings of iHOST implementation in context, including barriers and facilitators to uptake of different intervention components, how this is reflected in patient and provider perceptions of the intervention and outcome measures for each site.

### Difference-in-difference study

**
*Study design.*
** We will do a controlled study that will use data from iHOST hospitals and control hospitals (where iHOST is not implemented) to estimate the effect of iHOST on two outcomes: patient-directed discharge and emergency readmission within 28 days.

The study will use a difference-in-difference method
^
28,
29
^. This is a quasi-experimental design that aims to measure the effect of a change in clinical practice when the change in practice was not randomised. The method works by measuring patient outcomes in two groups (iHOST hospitals and control hospitals) and at two points in time. At the first point in time iHOST is not implemented in either group. At the second point in time, iHOST is only implemented in one group. The design is based on comparing the change in outcomes.

The purpose of including control hospitals is to account for background trends in outcomes that are common across hospitals. Examples include changes in the population (such as ageing), national policies, national restrictions related to COVID-19, and changes in drug supply. The design is more robust than an uncontrolled pre-post study, but less robust than a randomised experiment.

A central assumption of the difference-in-difference method is that there are common trends in the outcome across participants. In the absence of the intervention, we assume that the change in outcome observed in the control group would have happened in the intervention group. In
Figure 2, the ‘counterfactual iHOST’ risk is estimated using the trend in the control group, and the estimated effect of iHOST is the difference between the observed and counterfactual iHOST risks.

**Figure 2. f2:**
[figure not shown]
Illustrative difference-in-difference analysis.

**
*Population.*
** The study will use the Hospital Episode Statistics database, which includes all inpatient, outpatient, and A&E episodes at NHS hospitals in England
^
30
^.

The target population is hospital admissions for patients who may benefit from OST. Hospital Episode Statistics does not include records of OST (either in the community or in hospitals), and therefore the study will use a proxy of patients with records of opioid dependence. This will be defined as emergency hospital admissions (i.e., where the field ADMIMETH is 21-25, 2A, 2B, 2C, 2D, or 28) at acute hospitals in England, where the patient was (a) aged 18–64 years at admission; (b) the date of admission was between 12 months before and 12 months after the iHOST site’s implementation dates; and (c) the ICD-10 code F11 (‘mental and behavioural disorders due to use of opioids’) was recorded either at that admission or at another hospital episode for that patient in the preceding 12 months.

We will include patients from the three iHOST sites and from the 50 largest acute hospitals in England where iHOST is not being implemented (when size is defined by the number of patients meeting the criteria listed above). The reason for limiting the control group to the 50 largest hospitals is to exclude small hospitals that may have volatile trends in patient characteristics or outcomes.

**
*Analysis.*
** iHOST will be implemented at different times at each of the three participating hospitals. This means that background trends in outcomes could be different, and the analysis will therefore be done separately for each hospital.

For analysis of patient-directed discharge, study entry will be at hospital admission. For analysis of readmission, study entry will be at discharge, such that patients who died during the index admission are excluded. We will use a mixed (hierarchical) linear model in which the dependent variable is a binary indicator of the outcome, and independent variables are an interaction term between two binary outcomes: time (i.e., before/after iHOST implementation) and iHOST site or control; a random intercept for the hospital site; and patient-level confounders/covariates. This approach to modelling is known as a ‘linear probability model’, and we have selected it to allow estimation of absolute difference in the risk of outcomes. Confounders will be age, sex, season, primary cause of admission, number of comorbidities, proportion of patients at the hospital who have COVID-19. We will fit the model using a restricted maximum likelihood method implemented in the
R package
lme4
^
31
^. The effect of iHOST will be interpreted from the interaction between time and the control/intervention indicator. Definitions of study variables are included in Extended Data
^
32
^.

**
*Baseline data analysis.*
** We extracted data from Hospital Episode Statistics for the calendar year 2021 to estimate the number of eligible patients and understand their characteristics. The results are summarised in
Table 1. Hospitals are anonymised.

**Table 1. T1:** Number and characteristics of patients with recent diagnoses of opioid dependence in the calendar year 2021, based on preliminary analysis of Hospital Episode Statistics.

Site	Number of patients	Patient-directed discharge N (%)	28-day readmission N (%)	Age (IQR)	Male N (%)	5+ comorbidities N (%)	% patients at hospital with COVID-19
iHOST sites							
A	349	70 (20.1)	101 (28.9)	46 (36-54)	244 (69.9)	143 (41.0)	10.1
B	662	149 (22.5)	214 (32.3)	43 (38-47)	489 (73.9)	195 (29.5)	6.9
C	624	116 (18.6)	148 (23.7)	43 (37-50)	392 (62.8)	182 (29.2)	4.8
Control hospitals							
All	24604	4048 (16.5)	7001 (28.5)	43 (37-50)	16425 (66.8)	6718 (27.3)	7.9
1	893	61 (6.8)	322 (36.1)	42 (35-49)	535 (59.9)	97 (10.9)	6.1
2	818	102 (12.5)	156 (19.1)	40 (35-47)	584 (71.4)	138 (16.9)	8.3
3	728	103 (14.1)	183 (25.1)	45 (37-52)	458 (62.9)	134 (18.4)	9.0
4	732	191 (26.1)	265 (36.2)	45 (38-50)	533 (72.8)	208 (28.4)	6.7
5	739	92 (12.4)	249 (33.7)	43 (37-50)	445 (60.2)	185 (25.0)	5.8
Etc …							

**
*Power.*
** To estimate power, we simulated the study assuming that iHOST reduces the risk of each outcome by 5 percentage points (for example from 20% to 15%). For the “pre iHOST” data, we used the calendar year 2021 (summarised in
Table 2). For the "post iHOST” data, we used same dataset; but with outcomes randomly generated where the risk of each outcome was the hospital-specific risk from 2021, reduced by 5 percentage points for the iHOST sites. An example of a single simulation is shown in
Figure 3. We repeated this simulation 1,000 times and calculated the proportion of simulations in which a significant result was found (ie. p <0.05). This suggested good power to detect a risk reduction of 5 percentage points when results from the three hospitals are pooled, but low power at individual sites. Code for the power analysis is available at
https://github.com/[name]/ihost/tree/main/power.

**Table 2. T2:** Power of the iHOST study to detect an absolute reduction in outcomes of five percentage points.

	Patient-directed discharge	28-day emergency readmission
Site A	0.475	0.228
Site B	0.839	0.442
Site C	0.837	0.376
Pooled effect	>0.999	0.921

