### OST process measures

Participating hospitals will use local clinical data to report measures of the quality of OST provision (‘process measures’). We have worked with information specialists and clinicians at University College London Hospital NHS Foundation Trust to develop the following measures:

1. The number of patients administered methadone. Most patients provided with OST in acute hospitals in the UK are given methadone; and additionally, methadone is rarely given for other indications. Therefore, it is a useful indicator of the quantity of OST provided; while avoiding the need to consider the indication and formulation.2. Duration between decision to admit and administration of methadone, reported as (a) the proportion that is 24 hours or greater; and (b) the median and interquartile range.3. The dose, defined as (a) the proportion of patients administered at least 20mg of methadone in one 24-hour period; reported as a proportion of patients who are administered methadone and admitted for at least 24 hours, and (b) the mean and distribution of administered doses across 24-hour intervals following admission.4. The proportion of potentially eligible patients who are provided with OST, defined as the proportion of inpatients with a discharge diagnosis of ICD-10 F11 (‘opioid related disorders’) who were administered methadone or buprenorphine during their admission.5. The proportion of patients who are potentially eligible for OST who have a patient-directed discharge, defined as the proportion of inpatient admissions with discharge diagnosis of ICD-10 F11 (‘opioid related disorders’) that end in patient-directed discharge.6. Possible OST-associated overdoses, defined as inpatients who are administered naloxone after an administration of methadone or buprenorphine.

Depending on the feasibility of extracting these data, each iHOST site will calculate each measure for quarterly periods (i.e., every three months) for time periods before and during iHOST implementation. The sites will nominate a group of staff (for example medical staff, pharmacists, and information specialists) to review the indicators every three months. We will also do an uncontrolled before/after analysis to test if the indicators change after implementation of iHOST.

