**Controlled difference-in-difference study.** (a) No data will be available on OST prescriptions, either in the community or in hospital. Ideally, our study would include patients who had a community OST prescription prior to admission. Instead, we will use patients with a diagnosis of ‘opioid dependence’ as a group that may benefit from iHOST. This may dilute the effect of iHOST because some participants will not have prescriptions of OST; (b) the study will not capture any effect on patients’ propensity to seek treatment. Part of the rationale for iHOST is that people who are dependent on opioids avoid or delay hospital treatment because they anticipate poor OST. This study investigates outcomes after admission and will not capture any effect on patients’ propensity to seek treatment in hospital. If iHOST leads to more patients seeking hospital care or presenting earlier, this may cause residual confounding because patients after implementation will differ from those before; (c) The study will only estimate effects on patient-directed discharges and readmissions. These outcomes are based on previous research, patient and public involvement, and the availability of data in HES. Other important outcomes may be affected by iHOST, such as the quality of medical treatment, patient satisfaction, continuation of OST in the community, and use of illicit drugs. Other parts of the evaluation seek to understand broader outcomes. A more detailed list of limitations for the difference-in-difference study is provided in Extended Data
^
32
^.3. 
**OST process measures**. These measures are intended to support iHOST sites to learn about the quality of OST in their setting and identify opportunities for ongoing improvement. They are not a robust approach to estimating the impact of the intervention, as a change in these measures could be attributed to many factors other than the intervention, such as changing patient demographics, changing use of OST (eg. if iHOST leads to different types of patients being given OST), and wider healthcare policies.4. 

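### The cohort is selected on an F11 code that iHOST could plausibly change at its own sites after launch, so a shift in recording can bias the patient-directed discharge estimate in either direction

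*Protocol article*

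**What the plan says.** Hospital Episode Statistics holds no record of opioid substitution therapy (OST), and "therefore the study will use a proxy of patients with records of opioid dependence" (Protocol article, Difference-in-difference study, Population). The proxy is an F11 code that "was recorded either at that admission or at another hospital episode for that patient in the preceding 12 months". The same rule applies before and after launch and in all hospitals.

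Other sections bear on when and how that code arises:

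- OST process measures treats F11 as a code assigned at discharge; one indicator is "the proportion of inpatients with a discharge diagnosis of ICD-10 F11" who received OST. A second indicator has the same denominator. Staff at each iHOST site are "to review the indicators every three months".
- The intervention describes the online training: "The module aims to improve knowledge about opioid dependency and withdrawal and develop non-stigmatising care and communication practices". Of the card for patients on community OST it says: "Patients can give the card to hospital clinicians to facilitate OST".
- Under Analysis: "For analysis of patient-directed discharge, study entry will be at hospital admission". The listed confounders are age, sex, season, primary cause of admission, number of comorbidities and the hospital's COVID-19 proportion.
- The limitations in the Discussion say the proxy may dilute the effect, and that "If iHOST leads to more patients seeking hospital care or presenting earlier, this may cause residual confounding". They do not mention a change in how F11 is recorded. A longer list of limitations is in Extended Data, which is not shown.

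**The concern.** A difference-in-difference comparison needs cohort membership to mean the same thing before and after launch at the intervention sites, apart from changes shared with the controls. Here membership depends on a code that hospital staff generate, partly after the intervention has started and by staff whom the intervention trains. If F11 is recorded for more or different patients at iHOST sites after launch, the case mix of the post-launch cohort changes there and nowhere else. The interaction term then mixes changed care with changed recording.

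This differs from the two mechanisms that the protocol concedes. Dilution pulls a true effect towards zero, and changed care-seeking alters who comes to hospital. Changed recording alters who is counted among those who come, and it can move the estimate when care has had no effect. The power simulation reuses the same 2021 dataset for both periods, so it does not test a change in composition.

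**Working it through.** **When the qualifying code can be written.** For a pre-launch admission, the look-back lies wholly before launch. For an admission m months after launch (m up to 12), the code at the index admission is post-launch and so are m of the 12 look-back months: half of them at 6 months, all of them at 12. Exposure to iHOST-era recording is therefore built into the post-launch cohort.

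**What could offset it.** Controls remove trends common to all hospitals; a shift confined to iHOST sites is not common. No listed covariate measures recording practice, and the comorbidity count may itself depend on coding.

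**Baseline (Table 1).** The site percentages reproduce: 70/349 = 20.1%, 149/662 = 22.5%, 116/624 = 18.6%, controls 4048/24604 = 16.5%. Pooled iHOST sites: 335/1635 = 20.49%.

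**Effect of a recording shift when iHOST has no true effect.** Let newly coded admissions equal a fraction f of the existing cohort, with discharge risk r, and let p be the baseline risk.

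Apparent reduction = p − (p + f·r)/(1 + f) = [f/(1 + f)] × (p − r)

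No document gives f or r, so both are assumptions. The 10% value for r is the Introduction's approximate figure for people with a history of illicit opioid use. That figure is not limited to emergency admissions, so it is a rough anchor only.

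Pooled apparent reduction, in percentage points (negative = false increase):

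| r | f = 10% | f = 20% | f = 30% |
|---|---|---|---|
| 5% | 1.41 | 2.58 | 3.57 |
| 10% | 0.95 | 1.75 | 2.42 |
| 15% | 0.50 | 0.91 | 1.27 |
| 20.5% | 0 | 0 | 0 |
| 30% | −0.86 | −1.59 | −2.19 |

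Worked cell (f = 20%, r = 10%): (20.49 + 0.2 × 10)/1.2 = 18.74; 20.49 − 18.74 = 1.75.

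**Against the 5-point design effect.** At r = 10%, the range 0.95 to 2.42 is 19% to 48% of the target. Mimicking the full 5 points at r = 10% needs f = 5/(10.49 − 5) = 91%.

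**False-positive rate.** For the same cell, an unadjusted normal approximation gives SE = √[0.2049 × 0.7951/1635 + 0.1874 × 0.8126/1962 + 2 × 0.1645 × 0.8355/24604] = 1.37 points, where 1962 = 1.2 × 1635. Then 1.75/1.37 = 1.27, and the chance of two-sided p < 0.05 is about 25% instead of 5%. For f = 10% and 30% at r = 10% it is about 10% and 44%.

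**Where the sign turns.** Suppose a share x of the newly coded are patients who leave early and previously went uncoded (risk 100%), and the rest have 10% risk. The bias is zero when 0.10 + 0.90x = 0.205, that is x = 11.7%. With 5% risk for the rest, 0.05 + 0.95x = 0.205 gives x = 16.3%. Above those shares the bias hides benefit.

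**The case against.** The strongest reply is that the mechanism is inferred. The training is described in terms of knowledge, communication and stigma, not case-finding or diagnostic recording. The card is for people already receiving community OST, and some of them will already qualify through an F11 code from any NHS hospital in England in the previous 12 months. That share is not given, so the number newly captured could be small. This stands: the documents show that a shift is possible, not that it will happen.

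The adjustment for age, sex, primary cause and comorbidities may also absorb part of a case-mix change, and the illustration above is unadjusted. That stands as well.

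A further reply is that sensitivity cohorts are commonly left to an analysis plan and that Extended Data may discuss coding. That is fair as to omissions, but the point here is the cohort rule, which the article states in full. Listing a limitation would not separate recording from care in the estimate.

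Four stronger readings are tempting and are not supported:

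- A reader might infer that the design will produce a false reduction. The sign depends on who is newly coded, and a modest share of early leavers reverses it.
- A reader might extend a bias towards benefit to 28-day readmission. Nothing in the protocol gives its direction.
- A reader might treat inclusion that depends on the length or ending of the stay as a separate bias, since entry is at admission but the code comes later. Stable under-coding of early leavers, before and after launch and in controls, mainly affects which patients are studied. Only a differential change biases the interaction.
- A reader might call the bias as large as the target effect. At the protocol's own 10% figure, that needs 91% more coded admissions.

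**Conclusion.** The concern holds as a statement about what the design cannot rule out. The cohort rule admits codes written after iHOST starts, several iHOST-only components could plausibly influence those codes, and neither the controls nor the covariates clearly remove the result. The patient-directed discharge estimate can therefore be biased, in a direction the documents do not settle. A material shift is easy to construct: about 1.0 to 2.4 points of false reduction for 10% to 30% more admissions at 10% risk. These figures rest on assumed values of f and r, no true effect, no covariate adjustment and a rough anchor for r. Readmission has the same exposure, with no determinable direction.

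This does not invalidate the primary cohort, which is a reasonable proxy given the data. It does limit what a change in the primary result can be said to show unless recording is examined alongside it.

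**What to change.** Keep the current cohort as primary and pre-specify two additions.

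1. **Recording check.** Run the same difference-in-difference on the number of admissions coded F11 and on their share of emergency admissions. A differential rise could reflect care-seeking as well as recording, so it signals changed composition rather than proving its cause.
2. **Sensitivity cohort.** Define it identically in both periods and all hospitals by F11 codes that pre-date launch, for example F11 at an episode 12 to 36 months before the index admission. For any admission within 12 months after launch, a code at least 12 months older falls no later than the site's launch date.

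State in advance that a primary effect will be interpreted cautiously if recording shifts at iHOST sites or if the sensitivity estimate differs materially.

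The cost is a longer look-back extract from the same database, and a smaller cohort that omits recently coded patients. For scale, take the unadjusted normal approximation for a 5-point reduction (20.49% to 15.49%), with power = Φ(5/SE − 1.96):

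- All admissions: SE 1.38 points, pooled power about 0.95.
- 80% retained in every group (assumption): SE 1.54, power about 0.90.
- 50% retained in every group (assumption): SE 1.95, power about 0.73.

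This approximation from summary counts does not reproduce Table 2, which came from simulation on patient-level data, so it indicates only the relative loss. That loss of power, and the less current cohort, are why this analysis should support the primary analysis and not replace it.

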### The intervention

We will develop and evaluate an intervention (iHOST) to improve OST in acute hospital settings. iHOST will be implemented at three acute hospitals in England: University College London Hospital, St. James University Hospital Leeds, and Royal Stoke University Hospital. The project will be developed in partnership with local drug treatment services. The intervention primarily aims to improve continuation of OST from community to hospital settings but will also inform OST initiation and discharge planning for patients who were not already in receipt of community-based OST. The programme phases are shown in
Figure 1, and launch dates are currently anticipated to be:

University College London Hospital: November 2022 (already launched at the time of publication)St James University Hospital Leeds: January 2024Royal Stoke University Hospital: January 2024

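### The Analysis section specifies only separate single-hospital analyses, but the statement of good power rests on a pooled effect that it does not define

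*Protocol article*

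**What the plan says.** All of this is in the protocol article, mostly under Difference-in-difference study.

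- **Analysis, the rule.** The reasoning has three steps: "iHOST will be implemented at different times at each of the three participating hospitals"; "This means that background trends in outcomes could be different"; and so "the analysis will therefore be done separately for each hospital".
- **Analysis, the model.** A mixed linear probability model compares an iHOST site with controls, before and after launch. "The effect of iHOST will be interpreted from the interaction between time and the control/intervention indicator". No stacked model, meta-analysis or other combining step is mentioned.
- **Power.** The simulation assumes that "iHOST reduces the risk of each outcome by 5 percentage points (for example from 20% to 15"%), and the authors "calculated the proportion of simulations in which a significant result was found (ie. p <0.05"). They conclude that power is good "when results from the three hospitals are pooled, but low power at individual sites". Table 2 has one row per site and a row for a pooled effect. How that pooled effect is formed is not described.
- **The intervention, anticipated launch dates.** University College London Hospital is given as November 2022. The other two read "St James University Hospital Leeds: January 2024Royal Stoke University Hospital: January 2024".

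**The concern.** The analysis rule and the power claim concern different estimates. Following the rule gives six site-level results, three per outcome, and no overall one. The power that would reassure a reader attaches to an overall result that the Analysis section does not call for and whose stated reasoning points away from it.

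Two things are at stake. For readmission, each planned test is more likely than not to miss a true 5-point reduction, by the plan's own figures. And if pooling is decided only once results are in hand, the choice between a pooled headline and a site headline can be influenced by the data.

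The reason given for separating the sites is also loosely worded. Two of the three sites share an anticipated launch month, and different calendar windows do not prevent within-window estimates from being combined.

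**Working it through.** **1. The plan's own figures (Table 2, 5-point absolute reduction, p < 0.05)**

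| | Discharge | Readmission |
|---|---|---|
| Site A | 0.475 | 0.228 |
| Site B | 0.839 | 0.442 |
| Site C | 0.837 | 0.376 |
| Pooled | >0.999 | 0.921 |

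Four of the six site-level tests fall below 0.50. Two exceed 0.80.

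**2. What the separate tests deliver together.** Treat the sites as independent, which is approximate because controls are shared.

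- All three significant: discharge 0.475 × 0.839 × 0.837 = 0.33; readmission 0.228 × 0.442 × 0.376 = 0.04.
- At least one significant: discharge 1 − 0.525 × 0.161 × 0.163 = 0.99; readmission 1 − 0.772 × 0.558 × 0.624 = 0.73.

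So even if iHOST works equally well everywhere, a mixed set of site results is the likely outcome.

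**3. Independent check from Table 1.** Inputs: sites n = 349, 662, 624; discharges 70, 149, 116; readmissions 101, 214, 148; controls n = 24,604 with 4,048 and 7,001 events. Assume equal numbers before and after, a two-sided 5% test and no covariates. With p the 2021 risk, q = p − 0.05 and p_c the control risk:

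SE = √{[p(1−p) + q(1−q)]/n + 2p_c(1−p_c)/n_c}, power = Φ(0.05/SE − 1.96).

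Example, Site B readmission: p = 214/662 = 0.3233, q = 0.2733, p_c = 0.2845, SE = 0.0254, 0.05/SE = 1.966, power = Φ(0.006) = 0.50.

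| | Discharge | Readmission |
|---|---|---|
| Site A | 0.41 | 0.32 |
| Site B | 0.62 | 0.50 |
| Site C | 0.66 | 0.57 |
| Pooled (n = 1,635) | 0.95 | 0.89 |

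This does not reproduce Table 2. Variants (linear-probability SE, before-period data held fixed, simulation with hospital intercepts) move the figures, and no single one matches every cell. The real simulation used individual data, so this does not show Table 2 to be wrong. Every two-sided variant has the same pattern: pooled power at least 0.87, single-site readmission power at most 0.60.

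**4. Does the pooled row look like a combination of the site rows?** The simulation holds the 2021 data fixed and redraws only the after-period, so the test statistic varies with SD of about √0.5 = 0.707. Back-solve each site's expected z as 1.96 + 0.707 × Φ⁻¹(power), then combine by precision weighting under a common effect (root sum of squares).

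- Discharge: 1.916, 2.660, 2.654 → 4.218; Φ((4.218 − 1.96)/0.707) = 0.999, against >0.999 stated.
- Readmission: 1.433, 1.857, 1.737 → 2.918; Φ((2.918 − 1.96)/0.707) = 0.91, against 0.921 stated.

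The pooled row is therefore close to what a precision-weighted combination of the three site estimates would give. If the fixed before-period is ignored (SD = 1), the same steps give 0.996 and 0.78.

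**5. Launch dates against the stated reason.** November 2022 to January 2024 is 14 months. With 12 months either side, the first window runs November 2021 to November 2023 and the other two run January 2023 to January 2025. The first site does have its own background period. The other two share theirs. The windows overlap during most of 2023, when the same control admissions count as after-launch for the first site and before-launch for the others.

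**The case against.** The strongest reply is that the two sections need not conflict. Fitting each site separately and then pooling the results is an ordinary two-stage analysis. The Power paragraph and Table 2 both name a pooled effect, and an article may leave the formula to the analysis plan or to the power code. Site-specific effects are also meaningful in their own right: the Discussion says the intervention is fitted to each hospital, and that a clear effect on one primary outcome is not necessarily expected.

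Much of this stands. A reader might infer that the plan excludes pooling altogether, or that it hides a lack of power. Neither is supported: a pooled effect is named, site-level power is called low in plain terms, and discharge at Sites B and C is above 0.80.

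A reader might also cite a 26% chance of a false positive from six tests (1 − 0.95⁶). That assumes independent tests, whereas the two outcomes share admissions and the sites share controls, and the article nowhere says one significant result of six would count as success. How the two outcomes are tested is a matter of choice, and no particular multiplicity procedure is required here.

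Nor do the launch dates defeat the rationale. They are described as anticipated, and the first site's window really does differ.

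What the reply does not remove is that the Analysis section states a positive rule, with a reason, that stops at separate analyses, while the only adequate power for readmission belongs to a combined one. The formula could be left to an analysis plan. Whether an overall estimate is part of the analysis, and with what status, is fixed badly in the article itself.

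**Conclusion.** The concern holds as a mismatch between the Analysis and Power paragraphs. As written, the analysis has power of 0.228 to 0.442 for readmission at every site and 0.475 for discharge at Site A, against 0.921 and above 0.999 for the undefined pooled effect. Discharge at Sites B and C is adequately powered on the plan's figures.

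These sizes are Table 2's own and rest on its assumptions: a 5-point reduction at each site, 2021 patient numbers and a 0.05 threshold. The simplified recalculation supports the pattern but not each cell. The joint probabilities treat sites as independent. The launch-time sentence is a small wording error that does not affect these figures.

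**What to change.** In the Analysis section, add a pooled difference-in-difference estimate for each outcome as the main overall estimate, and say how it is formed. Either form would serve:

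- stack the three site cohorts in time since launch, each with its own period effect and contemporaneous controls, and estimate one common iHOST-by-period coefficient; or
- take a precision-weighted combination of the three site estimates, with a variance that allows for shared controls, including control admissions that fall in both calendar windows.

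Keep the site-specific estimates with confidence intervals, to show how effects differ across the tailored implementations. If only separate analyses are intended, rest the power statement on the site rows and say how three results per outcome will be read together. Reword the launch sentence to say that one site launched earlier and two are expected in the same month.

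The cost is a few sentences and one further model per outcome, with no new data. The downside is that a pooled effect averages over interventions that differ by site, which is why the site estimates should stay beside it. The change should be made before outcome results are seen.
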